## Abstract

There is no safe level of lead exposure. Correlations suggest that hunters harvesting wild game with lead bullets may be at risk of lead exposure through eating minute lead particles from shrapnel in their wild game. This feasibility study will determine if it is possible to conduct an interventional controlled, blinded study to evaluate if there is a causal relationship between meat harvested with lead bullets and elevated blood lead levels in those who consume the meat. This is an observational case crossover study and the primary outcome is blood lead levels. Individuals will have blood lead levels measured 2–4 days after eating one serving of meat harvested with lead bullets. At three potential washout periods these same individuals will have a subsequent blood lead level analysis. This observational study will provide the data necessary to determine the washout period and sample size for a prospective interventional study to evaluate if meat harvested with lead bullets raises blood-lead levels in those who consume the meat. This study has been approved by the Health and Disabilities Ethics Committees of New Zealand.

**Trial registration:**

NCT02775890.

## Introduction

1

As lead is one of the few substances that does not have a safe level of exposure, it is important to minimize all exposure [1], [2]. Hunters can use lead or lead-free bullets [3], and a vast majority choose to use lead bullets [4], [5], primarily because of tradition and the belief that lead bullets are safe. Non-lead projectiles are considered premium ammunition [6], but they are not significantly more expensive in some world areas [7]. There is a correlation between hunters using lead projectiles and elevated lead blood levels [8], [9], [10], however a causal link is unestablished [11]. As lead-shot meat is sold globally, this potential lead contamination is a global health concern [12].

This is a clinical research protocol to determine the feasibility of assessing lead levels in hunters who use lead projectiles. This observational study will determine if it is possible to perform a subsequent interventional blinded controlled study of lead levels in hunters using lead or lead-free projectiles following consumption of self-harvested wild game. The hypothesis for the subsequent study is that minute lead particles from shrapnel dispersed through the animal during harvest are ingested and this exposure results in increased lead blood levels [3]. This current observational study will establish the sample size and washout period for the subsequent interventional study. This observational study will be conducted in compliance with the protocol, Good Clinical Practice Standards, associated regulations and institutional research requirements.

There are three biological compartments where unexcreted lead is stored: blood, soft tissue, and mineralising tissues. After absorption, lead is stored in the blood compartment with a half-life of 28 [13] – 36 [14] days. Lead rapidly disperses into soft tissues post-exposure and in soft-tissues it has a half-life of approximately 40 days [15]. The primary long term repository of lead in the body is mineralizing tissue in bones and teeth [16]. Importantly, these mineralizing tissue stores can be mobilized and increase lead levels in the blood. The long half-life of lead and the dynamic nature of storage with the various compartments present challenges in identifying causal relationships between lead exposure and blood lead levels.

This current study establishes the parameters necessary to assess whether hunters eating meat shot with lead projectiles have elevated blood lead levels. For this feasibility study, hunters will be asked to abstain from consuming meat harvested with lead projectiles for 7 days. After 7 days, hunters will provide a baseline blood sample. Hunters will then consume meat that was harvested with lead projectiles and provide an additional blood sample 2–4 days (the blood-lead level peak post exposure [17]) after consumption. Hunters will also provide subsequent blood samples at periods of 9, 18, and 27 days. During the 27 day period, hunters will not consume meat harvested with lead projectiles. (Fig. 1). We have chosen to use deer as the species for this study to reduce variation; New Zealand is the ideal place to conduct this study because of year-round hunting of deer [18]. This study design will allow for the development of a conditional linear effects model, which will account for the inherent correlation of longitudinal data that involves repeated measures on the same subject over a period of time. A conditional model will also be more robust to any missing data that may arise through the course of the study, which may also facilitate a reduction in the required number of subjects necessary for this feasibility study.

**Fig. 1 fig1:**
[figure not shown]
**Design of the current feasibility study**. Participants in the current study will harvest deer with standard lead projectiles. A baseline lead measure, a measure immediately after eating the lead-shot meat, and measures at 9, 18 and 27 days. These blood lead levels will allow a model to be built determining appropriate sample size for each potential washout period.

If this current observational study determines that an interventional study is feasible, the subsequent interventional study would randomize hunters into two groups: hunters using lead projectiles and hunters using non-lead projectiles. All hunters would undergo an initial wash-out period and then have baseline blood lead level recorded. Hunters in both cohorts would then eat the harvested meat and blood lead levels would be recorded 2–4 days after eating the self-harvested meat. Hunters would then repeat this process for a replication of 3 times during the year. After one year, the hunter would cross over to the other type of projectile and repeat the entire process again (Fig. 2). This case crossover study would be analyzed utilizing a conditional linear effects model to account for the correlative nature of longitudinal data involving repeated measures. Additionally, this model will allow for other factors to be included in the model, including time-dependent covariates. Additionally it would be possible to use isotope analysis to identify if the lead levels in the blood of participants were primarily from the environment or from the lead projectiles [10], [19]. Fortunately, baseline blood lead levels in New Zealand are similar to levels in other developed countries [20] thus allowing a broad extrapolation of the data generated.

**Fig. 2 fig2:**
[figure not shown]
**Design of the proposed subsequent crossover study**. Participants in the subsequent study will be randomized to the lead or lead-free projectile arm of the study. After one year these participants will cross over to the other arm. Washout period and sample size will be determined by the results of the current feasibility study.

## Material and methods

2

### Study objectives

2.1

The primary objective of this observational study is to determine the washout period and sample size for a subsequent study measuring lead levels in hunters in New Zealand after eating wild game shot with lead projectiles. This primary objective will be accomplished through measuring lead levels in hunters who have recently eaten meat harvested from deer killed with lead projectiles and subsequently measuring blood lead levels of those same hunters after abstaining from eating meat harvested from deer killed with lead projectiles (Fig. 1).

The secondary objective is to determine the feasibility of a blinded controlled interventional trial comparing blood lead levels in hunters using lead and lead-free projectiles for harvesting wild game for consumption. Specifically, this aspect of feasibility will be determined by participant compliance during this feasibility study.

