### General study design

2.2

There are two periods of analysis for this study.1.Hunters that within 2–4 days prior to blood being drawn have eaten self-harvested wild deer shot with lead projectiles; and2.Hunters that have abstained from eating self-harvested wild deer shot with lead projectiles for specific periods of time.

Hunters in period 1 and period 2 are the same individuals; they will be consented for the study once they have harvested an animal and provide pictures of shot placement. In order to avoid bias, the investigator performing the data analyses and the laboratory staff will be blinded to the samples. The participants will know when they are submitting blood samples during the period while eating meat harvested with lead bullets and when they are submitting blood samples while abstaining from lead-harvested meat so they will not be blinded. Animals will be shot in the thorax (Fig. 3) and the hunter will provide photographs of the shot location. Hunters should process the animal according to their standard practice, including making of minced meat.

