**Fig. 4 fig4:**
[figure not shown]
**Resource created for hunters interested in participating in the study.** For outreach and to facilitate participant recruitment, bi-fold business-card sized information sheets that can be kept with the potential participant's firearms license are being created. The front and the back of the resource is shown.

It will be explained to hunters that after they shoot an animal that they must take a photograph of the animal to document shot placement. The photograph will be at least 72dpi resolution and clearly identify the location the animal was shot. The hunters must provide the weight of their bullet (brand if possible) and number of shots used to harvest the animal. This step is important to verify shot placement, and also to confirm the ability of the prospective participant to follow the directions for the study. The pictures indicating shot placement will be emailed to [contact] with the hunter contact information and a time available for a phone call. All hunters that send pictures will receive a phone call from the study coordinator.2.Consent to enrol in study

Hunters that successfully email photographs of the harvested animals with the required information will be interviewed by the study coordinator for enrollment in the study. Enrollment in the study will occur in two steps. First, a telephone call will explain to the participant the consent form (see supplemental data) and answer questions the participant has regarding the study. The participant will be asked approximately how many times per week they eat lead-shot animals and if they are willing to abstain from eating lead-shot meat for 9, 18, or 27 days. Second, if the participant is still interested in participating, a consent form will be mailed to the participant and a time will be scheduled for a subsequent telephone call to allow formal consenting of the participant. Preliminary discussions with hunters have determined that a majority would be willing to abstain from eating wild-shot meat for one month for the study. However, if hunters decline to participate based on the length of abstaining from eating wild meat, they will be offered to still participate and abstain from eating lead-shot meat for 9 days (or the maximum they are willing to abstain). The consent form package will include a postage-paid envelope.

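### Compliance in pre-screened, lead-only hunters can support feasibility of the meal, abstention and blood-draw procedures, but not of the assigned-projectile, two-year crossover that Section 2.1 lets it decide

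*Protocol article*

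**What the plan says.** Section 2.1 states: "The secondary objective is to determine the feasibility of a blinded controlled interventional trial comparing blood lead levels in hunters using lead and lead-free projectiles". The next sentence gives the criterion: "Specifically, this aspect of feasibility will be determined by participant compliance during this feasibility study". The Introduction makes the later trial conditional on this study finding it feasible, and the Discussion describes that trial as larger and more expensive.

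Who is observed:

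- Section 2.5, step 1, asks hunters to photograph the shot placement and to supply bullet weight and number of shots. One stated purpose is "also to confirm the ability of the prospective participant to follow the directions for the study".
- Step 2 continues: "Hunters that successfully email photographs of the harvested animals with the required information will be interviewed by the study coordinator for enrollment in the study". Section 2.2 places consent after the harvest and the photographs.
- Also in step 2, hunters who decline because of the length of abstention may still take part and "abstain from eating lead-shot meat for 9 days (or the maximum they are willing to abstain").

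What they do: the Fig. 1 legend has every participant harvesting with standard lead projectiles. Section 2.5, step 3, describes a baseline sample, a test meal, a draw 2–4 days later, and draws at 9, 18 and 27 days. Section 2.2 blinds the analyst and the laboratory to the samples. Participants know when they give blood after the meal and when they give it "while abstaining from lead-harvested meat so they will not be blinded".

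What the later trial asks: hunters are randomised to a projectile type and the meal cycle is done three times in the year. The Introduction then adds: "After one year, the hunter would cross over to the other type of projectile and repeat the entire process again".

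Section 2.7 also classifies hunters as agreeing, declining because of abstention, or declining for another reason, in order to choose a feasible abstention length.

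**The concern.** The criterion does not match the question. Hunters are admitted partly on evidence that they follow directions, and the study then measures how well they follow directions. Some are allowed an easier task. None does the things that set the later trial apart, namely shooting with a projectile someone else has chosen and staying through repeated cycles for two years.

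Read as written, Section 2.1 would let high compliance stand as evidence that the crossover can be done. The decision to start the larger trial could then rest on a result this design cannot supply.

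**Working it through.** The plan gives no compliance rate and no pass rate for the photograph step, so there is no stated figure to reproduce. The check sets the two studies side by side and then asks which way each selection rule pushes.

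**1. What compliance here can inform**

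| Element | This study | Later trial | Informed by compliance here? |
|---|---|---|---|
| Test meal, abstention, blood draws | One cycle | Repeated cycles | Yes, for one cycle |
| Projectile | Lead for all, not assigned | Randomised, then the other type | No |
| Number of cycles | 1 | 3 × 2 = 6 (the Discussion says at least three a year) | No |
| Duration | 7 + 27 = 34 days; 7 + 4 + 27 = 38 if the 27 days run from the latest post-meal draw | Two years | No |
| Analyst and laboratory blinding | Yes, to the samples | Called blinded, no detail | The procedure is exercised |
| Hunters blinded to projectile | No | Not stated | Open |

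Inputs: Introduction, Fig. 1 and Fig. 2 legends, Sections 2.2 and 2.5, Discussion.

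**2. Direction of the photograph screen**

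Let p be the share of interested hunters who pass the step, and let C_pass and C_fail be the compliance of those who pass and of those who would have failed. Compliance among all is p·C_pass + (1 − p)·C_fail, so

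C_pass − C_all = (1 − p)·(C_pass − C_fail).

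This is positive whenever hunters who pass comply better than those who do not, and the protocol's own reason for the step supposes that they do. The documents give none of p, C_pass or C_fail, so the size cannot be computed.

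**3. Effect of self-chosen abstention**

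Let f be the share of enrolled hunters who agreed to the full schedule, and c the proportion who complete what they agreed to, taken as equal in both groups. If finishing an agreed short abstention counts as compliance, the reported figure is f·c + (1 − f)·c = c. Against the full schedule it is f·c. All values below are assumed, for illustration only:

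| f | c = 0.90: reported 90%, full schedule | c = 0.75: reported 75%, full schedule |
|---|---|---|
| 0.5 | 0.5 × 0.90 = 45% | 0.5 × 0.75 = 37.5% |
| 0.7 | 0.7 × 0.90 = 63% | 0.7 × 0.75 = 52.5% |
| 0.9 | 0.9 × 0.90 = 81% | 0.9 × 0.75 = 67.5% |

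The article does not say whether a short abstention would be counted this way. The table shows only that the answer matters. Section 2.5 reports that a majority of hunters in preliminary discussions would abstain for one month, which points to f above one half but fixes no value.

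**4. What Section 2.7 recovers**

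The refusal variable captures hunters who decline because of abstention, so part of the second selection is visible. It has no category for a hunter who declines the long period and then joins for a shorter one, it does not reach hunters lost at the photograph step, and its stated use is to choose the washout length.

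**The case against.** The other side has a good deal of force.

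- *The lead-free arm is deferred openly.* The Discussion reports the suggestion to include one and explains why it is left to the later trial. That choice is reasonable, and a feasibility study need not rehearse everything. This stands, but deferring an element does not turn compliance without it into evidence about it.
- *Compliance is not the only feasibility evidence.* Section 2.1 speaks of one aspect of feasibility; sample size, washout and the Section 2.7 refusal table also contribute. This stands. The point concerns only what 2.1 attaches to compliance.
- *An operational definition of compliance may sit in the full protocol.* This also stands, and its absence from the article is not the complaint. Even a strict definition would leave assignment and two-year participation unobserved.
- *The later trial might use the same photograph screen before randomisation.* The documents do not exclude it. If it did, the enrolled hunters would be the relevant group and the first source of overstatement would fall away. The second source and the mismatch of tasks would remain.

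A reader might infer four stronger things, which the documents do not support:

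- *Blinding goes wholly untested.* Analyst and laboratory blinding is exercised here (Sections 2.2 and 2.5), and nothing says that hunters in the later trial would be blinded to their projectile.
- *Failed shots and missing photographs would become losses after randomisation.* The descriptions of the later trial state no shot-placement or photograph requirement.
- *Only hunters with a valid photograph are telephoned.* Section 2.5 promises a call to everyone who sends pictures; it is the enrolment interview that is restricted.
- *True compliance can be found by dividing completers by all interested hunters.* Planned attrition gives 68 × 0.75 = 51 completers, but 51 over an assumed pool of interested hunters is recruitment yield. A hunter who shot no deer or never volunteered has not failed to comply.

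**Conclusion.** The point holds in a limited form. As the criterion in Section 2.1, compliance is likely overstated for the purpose it is given, and it carries no information on accepting a randomly assigned projectile or on three meal cycles a year over two years.

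The direction of the overstatement rests on two assumptions: that hunters who pass the photograph step comply better than those who do not, and that completing a shortened abstention would be counted as compliance. Its size cannot be derived from the documents, and the illustrative percentages are not estimates. The absence of information on assignment and duration rests on no assumption; it follows from the two designs as described.

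This is a secondary objective, and the washout and sample-size objective is unaffected. It still deserves correction, because the Introduction ties the start of the later trial to a feasibility finding.

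**What to change.** 1. Reword Section 2.1 so that compliance supports feasibility of the meal, abstention and blood-draw procedures only. Suggested text: *Compliance will be used to judge the feasibility of the test meal, the abstention and the blood draws. It will not be taken as evidence that hunters would accept a randomly assigned projectile or take part for two years.*
2. In the telephone interview already planned in Section 2.5, step 2, ask whether the hunter would accept a randomly assigned projectile and two years with three meal cycles a year. Ask about blinding to projectile only if the later trial is to blind hunters. The answers are stated willingness and should be reported as such.
3. Under the compliance outcome in Section 2.3, report compliance against the full 9/18/27-day schedule. Show hunters enrolled for a shorter abstention as a separate category, not counted as meeting it, and give them their own category in the Section 2.7 refusal table.
4. Report the flow from hunters who send photographs or otherwise make contact, through valid photograph, consent, baseline and meal, to each draw. Present it as recruitment yield alongside compliance, not as the compliance denominator. Because recruitment runs through clubs and social media, hunters lost before any contact will stay uncounted, and the report should say so.

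The cost is a slightly longer call, a simple log and some wording, with no new arm, visit or blood draw. The downside is a less favourable feasibility statement.

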### General study design

2.2

There are two periods of analysis for this study.1.Hunters that within 2–4 days prior to blood being drawn have eaten self-harvested wild deer shot with lead projectiles; and2.Hunters that have abstained from eating self-harvested wild deer shot with lead projectiles for specific periods of time.

Hunters in period 1 and period 2 are the same individuals; they will be consented for the study once they have harvested an animal and provide pictures of shot placement. In order to avoid bias, the investigator performing the data analyses and the laboratory staff will be blinded to the samples. The participants will know when they are submitting blood samples during the period while eating meat harvested with lead bullets and when they are submitting blood samples while abstaining from lead-harvested meat so they will not be blinded. Animals will be shot in the thorax (Fig. 3) and the hunter will provide photographs of the shot location. Hunters should process the animal according to their standard practice, including making of minced meat.

**Fig. 3 fig3:**
[figure not shown]
**Required shot placement for participation in the study**. Animals harvested for this study will be shot in the area indicated by a red box. This shot placement will be validated by photographs submitted to the study coordinator and will be the primary qualifying criteria for participating in the study. (For interpretation of the references to colour in this figure legend, the reader is referred to the web version of this article.)

Meals can be prepared at individual discretion; however, the meal must include at least 85 g of minced meat per test subject. This is equivalent to ¾ cup of minced meat and is considered a standard serving. Minced meat is used to reduce variability and allow easy determination of meal portion size. This value was used as the basis of the sample size calculation.

### Outcome variables

2.3

The primary outcome variable for the study is blood lead levels and the secondary outcomes include: compliance with study protocol; measures of complete blood count; mass of lead projectile; and number of shots fired.

### Inclusion and exclusion criteria

2.4

To be included in this study, participants must be over 18 years old and eat minced meat from the animals they harvest. Exclusion criteria are listed in Table 1.

**Table 1 tbl1:** Exclusion criteria for the study include any activities that may increase the basal blood lead level.

Smoker
Any type of kidney dysfunction
Any mineralising tissue fracture
Pregnant women
Menopausal women
Individuals working in the following industries that may entail lead exposure:
a) lead–acid battery manufacture
b) lead smelting
c) non-ferrous smelting and casting (e.g. brass)
d) steel scrap smelting
e) scrap lead metal handling
f) cutting/welding steel scrap
g) machining or polishing lead-containing alloys
h) plastic production (where lead compounds are used as stabilisers)
i) demolition
j) lead soldering
k) plastic recycling
l) panel beating
m) paint removal
n) sandblasting
o) leadlight window manufacture
p) lead casting, e.g. fishing weights, toy soldiers
q) radiator repair,
r) car exhaust repair and engine reconditioning (for older makes and models of vehicles)
s) jewellery (silver) production
t) shooting range

